## Methods

Patients are selected according to the following criteria:Inclusion criteria:Patients between 18 and 69 years oldSurgical laparoscopic approach for AAIntra-operative and histological diagnosis of AAExclusion criteria:Patients < 18 years old or > 69 years oldPrevious appendectomyPrevious appendicitis treated conservativelyOpen approach for surgery or intra-operative conversionCo-existence of other intra-abdominal infections (IAI)Patients with immunodeficiencyPatients treated with steroid, immunosuppressant, or CHT within previous 6 months

Clinical data:Patient IDDemographic data (age, sex, BMI)Comorbidity (American Society of Anesthesiology classification, Charlson comorbidity index [18])Organ failure at admission (predisposition infection/injury response organ dysfunction—PIRO score [19])Alvarado score and CRP

Operative data:Lavage and suction vs suction aloneLavage volumeDrainageOperative timeOperator: resident (under senior surgeon supervision) vs senior surgeonIndividual difficulty grading scale of the procedure

Intra-operative findings:Grade of appendicitis according to classification (see below)Corresponding histology gradePresence of single or multiple abscessesPresence of localized or diffuse, purulent, or fecal peritonitis

Postoperative data and follow-up:Overall length of stayLength of stay in ICUAntibiotic therapyDuration of antibiotic therapySuperficial surgical site infectionDeep surgical site infectionSurgical site infection organ/space infectionSingle intra-abdominal collectionMultiple intra-abdominal collectionsPeritonitisClavien-Dindo Classification of surgical complications [20]New access in ED with diagnosis of IAA into 30–60–90 daysLength of stay for new hospitalization

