## Hypothesis, design of the study, and aims

The driving hypothesis of our study is that there should exist a relationship between different intra-operative treatment protocols (irrigation vs suction alone) and postoperative incidence of IAA. Furthermore, considering various grades of appendicitis and peritoneal contamination, the use of irrigation vs suction alone could lead to different rates of postoperative IAA.

The aim of this study is to introduce and evaluate a classification for acute appendicitis taking into account the peritoneal contamination to delineate the relationship between grade of appendicitis and postoperative incidence of IAA considering the surgeon’s attitude toward irrigation or suction alone. Some studies described that the incidence of postoperative IAA is higher in the perforated appendix [12, 13]. No clear evidence exists exploring the severity of peritonitis as a potential predictor of IAA and its relationship with irrigation or suction alone.

This is a prospective observational multicenter study.

Primary endpoint:Relationship among each severity grade of acute appendicitis and postoperative incidence of intra-abdominal abscesses

Secondary endpoint:Impact of intraperitoneal irrigation or suction alone on the incidence of IAA for each severity grade

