### Data collection and statistical analysis

Participants will fill an online form reporting all clinical and intra-operative data of each patient who will undergo a laparoscopic appendectomy. All personal information of patients will be removed according to data anonymization.

Data will be reported in accordance with Strengthening the Reporting of Observational studies in Epidemiology guidelines (STROBE) for observational studies [22].

Residents from each involved center will be responsible for data collection.

All forms will be collected in an electronic database by the coordinating residents who will check for data completeness. All residents taking part in the study will be asked to enter eventual missing data.

The incidence of IAA after laparoscopic appendectomy reported in the literature ranges from 1.5 to 20% [4, 5, 9–11]. Such a wide interval is not negligible when calculating the sample size (*n*) of the study cohort. Furthermore, some important basic considerations need to be taken into account: appendicitis is the most common acute surgical disease so the baseline population is large and cannot be exactly estimated; the incidence of intra-abdominal abscesses has never been systematically investigated in regard to the severity of appendicitis and contamination. All patients included in the study will be classified into different clusters considering the grade of appendicitis and contamination, lavage vs suction alone, and postoperative incidence of IAA.

Considering all these aspects, sample size for power calculation can be reasonably estimated given a 95% confidence interval with a *z*-score of 1.96, a 50% standard deviation, and a 0.03 margin of error. This formula does not include the incidence rate of IAA for the aforementioned reasons.

The estimated sample size would be around at least 1067 patients. Data will be collected in a computerized spreadsheet (Microsoft Excel 2016; Microsoft Corporation, Redmond; WA) and analyzed with statistical software (IBM Corp. Released 2017. IBM SPSS Statistics for Windows, version 25.0. Armonk, NY).

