## Discussion

The observational nature of this study is mandatory to examine and analyze surgeon attitude toward peritoneal contamination related to appendicitis during laparoscopic appendectomy. The optimal study design to address the core matter would be a well-structured RCT to assess the real effect of lavage plus suction versus suction alone on postoperative IAA. As above reported in the “Introduction, background, and rationale” section, there is a lack of methodological strictness in the existent randomized trials due to heterogeneous determination of appendicitis severity and peritoneal contamination.

We feel indispensable to start from identifying different grades of appendicitis, related contamination, and their relationship with postoperative abscesses, considering surgeons’ attitude. The core step is to classify each patient and create a score to pick out classes of peri-appendiceal contamination related to different incidence rate of postoperative IAA.

The General Surgery residency program at the University of Milan is based on a large clinical network in which residents are distributed in different hospitals. It is a 5-year program. One hundred thirty residents are involved. The clinical network includes 59 surgical units in 27 hospitals.

This system structure allows great exposure to different surgical scenarios, inside and outside the operating room. The program requires, per year, a minimum of procedures in which the resident has to be involved. From the first to the fifth year, the difficulty of the procedure is increased. To the best of our knowledge, this is one of the most efficient residency programs in Italy because great attention is dedicated to surgical skills improvement. On the other hand, this program may underestimate the scientific needs and educational growth of residents. This study is resident driven as an incitement to a defined organization for the scientific growth of the University of Milan residents.

During the project start-up phase of this study, an official group of residents of the General Surgery program at the University of Milan has been created. The main aim of this group of young doctors is to try to guarantee to each resident, who is interested, the minimal scientific knowledge and ability to critically understand, ideate, and project a scientific study.

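### Surgeon attitude to irrigation is in the aim and justifies the design, but the listed data identify the operator only by seniority, so individual habit and surgeon clustering are out of reach

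*Protocol article*

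**What the plan says.** - **Aim.** In *Hypothesis, design of the study, and aims* the protocol article sets out to relate grade of appendicitis to postoperative intra-abdominal abscess (IAA) "considering the surgeon’s attitude toward irrigation or suction alone". The secondary endpoint there is the effect of irrigation or suction alone on IAA within each severity grade.
- **Reason for the design.** The Discussion says that the observational design is "mandatory to examine and analyze surgeon attitude toward peritoneal contamination". The Discussion part of the Abstract says much the same. The Discussion also concedes that a randomised trial would be the best design for the lavage question itself.
- **Data on the operator.** In Methods, under operative data, the operator is recorded as "resident (under senior surgeon supervision) vs senior" surgeon. The list includes a patient ID but no surgeon, unit or hospital code.
- **Data on the case.** Lavage versus suction alone, lavage volume and a difficulty grading are recorded per patient. So are histology, abscesses, type of peritonitis and "Grade of appendicitis according to classification (see below").
- **Data flow.** Under *Data collection and statistical analysis*, residents at each centre complete the forms and are asked to supply missing items. Patients' personal information is removed.
- **Analysis.** The same section plans chi-square tests, then univariate and multivariate regression. It states no centre or surgeon term and no variance adjustment for clustering.
- **Possible clusters.** "The clinical network includes 59 surgical units in 27 hospitals", and "One hundred thirty residents are involved".

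**The concern.** Attitude to irrigation is a property of a surgeon, or of the unit that trained the surgeon. Seniority does not measure it: two senior surgeons may irrigate almost always and almost never. For a supervised case, the field does not show whose preference decided the lavage.

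Two things are at stake, both for the secondary endpoint.

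1. **Description and confounding.** Irrigation is not randomised, and surgeons may irrigate dirtier fields more often. Adjusting for recorded grade and contamination leaves severity within a grade uncontrolled. Variation between surgeons with different habits depends less on the individual case, so it gives a useful second view of the comparison. Without a surgeon code that view is unavailable, even as a sensitivity analysis.
2. **Precision.** If irrigation is concentrated in certain surgeons or centres, and IAA rates also differ between them, standard errors that treat patients as independent are too small.

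The choice of model could be left to an analysis plan. The identifier could not, because no model can use a cluster that was never recorded.

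**Working it through.** **1. The plan's own figure.** Inputs from *Data collection and statistical analysis*: z = 1.96, "a 50% standard deviation, and a 0.03 margin of error". The formula for the precision of one proportion gives

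n = z² p(1 − p) / e² = 1.96² × 0.25 / 0.03² = 1067.1.

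This reproduces the stated figure ("The estimated sample size would be around at least 1067 patients"). It treats all patients as independent.

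**2. What the listed fields allow.**

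| Question | Possible from the listed fields? |
|---|---|
| Irrigation rate by grade, contamination, difficulty, seniority | Yes |
| Irrigation effect adjusted for recorded severity | Yes |
| Irrigation rate by hospital | Not listed; perhaps recoverable from who files the form |
| Irrigation rate by individual surgeon | No |
| Surgeon preference separated from unmeasured severity within a grade | No |
| Allowance for clustering by surgeon | No |

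**3. Size of the clustering effect on the irrigation comparison.** For an exposure that itself clusters, an approximate design effect is

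DE = 1 + (m − 1) × ICC(irrigation) × ICC(IAA),

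where m is the number of patients per cluster, taken as equal across clusters. The documents give neither intraclass correlation (ICC). I assume 0.3 to 0.6 for irrigation and 0.02 to 0.05 for IAA, so the product runs from 0.3 × 0.02 = 0.006 to 0.6 × 0.05 = 0.03. Cluster counts are the 59 units and 27 hospitals in the Discussion. The number of operating surgeons is not given, so the 130 residents serve only as a stand-in for it.

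- Units: m = 1067/59 = 18.1. DE = 1 + 17.1 × 0.006 = 1.10 to 1 + 17.1 × 0.03 = 1.51.
- Hospitals: m = 1067/27 = 39.5. DE = 1 + 38.5 × 0.006 = 1.23 to 1 + 38.5 × 0.03 = 2.16.
- Surgeons: m = 1067/130 = 8.2. DE = 1 + 7.2 × 0.006 = 1.04 to 1 + 7.2 × 0.03 = 1.22.

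The naive standard error is too small by the fraction 1 − 1/√DE. The true level of a nominal 5% test is 2 × P(Z > 1.96/√DE).

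| Level | DE | Naive SE too small by | Actual level of a 5% test |
|---|---|---|---|
| Unit | 1.10 to 1.51 | 5% to 19% | 6.2% to 11.1% |
| Hospital | 1.23 to 2.16 | 10% to 32% | 7.7% to 18.2% |
| Surgeon (if about 130) | 1.04 to 1.22 | 2% to 9% | 5.5% to 7.6% |

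The larger figures belong to the hospital level, where the identifier is most likely to be recoverable. At the surgeon level, where it is not, the effect on precision is modest under these assumptions. If fewer units or hospitals take part than the network contains, m and DE rise.

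**The case against.** The strongest reply is that a journal article condenses the form. Administrative identifiers are often left out of such a list, and this one names no date of surgery although it has 30-, 60- and 90-day follow-up. That stands: the article shows that the code is not listed, not that it will not exist. A reader might infer an irreparable gap, and the document does not support that.

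Other points on that side also stand.

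- The centre is probably traceable, because its residents file the forms and answer queries about them. A reader might take the anonymisation as destroying surgeon and centre information, but the text removes only patients' personal information.
- Attitude could mean the choice made for a given degree of contamination, which is recorded per patient. No endpoint names individual surgeons' habits. A reader might conclude that practice cannot be described or adjusted for severity at all. That goes too far: aggregate practice can be described, and recorded severity can be adjusted for.
- A reader might quote 18% false positives as the cost of the missing surgeon code. That is the upper hospital-level figure on assumed ICCs.
- A comparison based on surgeon habit has its own confounders, such as skill and the use of drains or antibiotics, and would be imprecise with few patients per surgeon.

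What the reply does not remove is the mismatch. The list is detailed enough to include lavage volume and the length of a later hospital stay. The aim and the reason for the design invoke the surgeon, yet the only operator attribute is seniority. Nothing shown makes the operating surgeon recoverable.

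**Conclusion.** The point holds as a mismatch between the stated purpose and the listed data, coupled with an analysis that states no allowance for clustering in a multicentre study. Followed as written, the plan can describe irrigation by grade, difficulty and seniority. It cannot describe individual surgeons' habit, separate that habit from unmeasured severity within a grade, or allow for surgeon clustering in the irrigation comparison. Centre clustering could probably be handled, but the article does not say that it will be.

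The loss of the surgeon-level view matters more than the surgeon-level variance effect, whose illustrative range is small. All the design effects rest on assumed ICCs, equal cluster sizes, full participation of the network and, for surgeons, a count of about 130. They apply to the secondary endpoint. They do not apply to the primary relation between grade and IAA, and they do not show the figure of 1067 to be miscalculated.

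**What to change.** First confirm whether the online form already holds surgeon and centre identifiers. If it does, say so in Methods. If it does not:

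1. Add to the operative data a pseudonymous code for the operating surgeon and one for the unit or hospital, with the key kept at the centre.
2. Report the irrigation rate by surgeon or centre and by grade, as the description of attitude.
3. Under *Data collection and statistical analysis*, fit the irrigation comparison with a random effect or cluster-robust errors for centre, and for surgeon where numbers allow.

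The cost is two or three coded fields, a slightly higher chance that a surgeon could be identified (which the pseudonymous codes limit), and somewhat wider intervals. The codes are easy to collect prospectively and hard to reconstruct afterwards.

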### Classification

Our proposal of classification (Table 1) is based on both the histological grade [21] of appendicitis and intra-operative degree of peritoneal contamination, considering data collected from the literature.

**Table 1 Tab1:** Proposal of classification

Appendix aspect	
Erythematous and edematous appendix^a^	
Appendiceal phlegmon^b^	
Gangrenous appendix^c^	
Perforated appendix^d^	
Contamination	
Single abscess	
Multiple abscesses	
Localized purulent peritonitis	
Diffuse purulent peritonitis	
Localized fecal peritonitis	
Diffuse fecal peritonitis	

^a^Neutrophils within mucosa and submucosa with mucosal

^b^Neutrophilic infiltration of mucosa, submucosa, and muscolaris propria. Transmural inflammation, extensive ulceration, and intramural abscess; vascular thrombosis

^c^Transmural inflammation with areas of necrosis; extensive mucosal ulceration

^d^Transmural inflammation with areas of necrosis; extensive mucosal ulceration plus parietal disruption [17]

One type of appendix aspect will be assigned to each patient, as well as one type of contamination will correspond to a single patient.

### Data collection and statistical analysis

Participants will fill an online form reporting all clinical and intra-operative data of each patient who will undergo a laparoscopic appendectomy. All personal information of patients will be removed according to data anonymization.

Data will be reported in accordance with Strengthening the Reporting of Observational studies in Epidemiology guidelines (STROBE) for observational studies [22].

Residents from each involved center will be responsible for data collection.

All forms will be collected in an electronic database by the coordinating residents who will check for data completeness. All residents taking part in the study will be asked to enter eventual missing data.

The incidence of IAA after laparoscopic appendectomy reported in the literature ranges from 1.5 to 20% [4, 5, 9–11]. Such a wide interval is not negligible when calculating the sample size (*n*) of the study cohort. Furthermore, some important basic considerations need to be taken into account: appendicitis is the most common acute surgical disease so the baseline population is large and cannot be exactly estimated; the incidence of intra-abdominal abscesses has never been systematically investigated in regard to the severity of appendicitis and contamination. All patients included in the study will be classified into different clusters considering the grade of appendicitis and contamination, lavage vs suction alone, and postoperative incidence of IAA.

Considering all these aspects, sample size for power calculation can be reasonably estimated given a 95% confidence interval with a *z*-score of 1.96, a 50% standard deviation, and a 0.03 margin of error. This formula does not include the incidence rate of IAA for the aforementioned reasons.

The estimated sample size would be around at least 1067 patients. Data will be collected in a computerized spreadsheet (Microsoft Excel 2016; Microsoft Corporation, Redmond; WA) and analyzed with statistical software (IBM Corp. Released 2017. IBM SPSS Statistics for Windows, version 25.0. Armonk, NY).

*χ*^*2*^ test will be assessed to compare categorical variables, and univariate logistic regression will be performed to provide hazard ratios for individual variables, identifying possible predictors of postoperative complication (IAA above all). All significant (*p* < 0.05) variables at univariate analysis will be included in a multivariate regression model in order to detect independent risk factors for the outcome and to estimate odds ratio and 95% confidence intervals.

A scoring system will be built according to the results of statistical analysis. The weight of each variable will be addressed based on odds ratio values. To evaluate the accuracy of the score, discrimination and calibration of the model will be explored. The former will be assessed by receiver operating characteristic (ROC) curve analysis, whereas the latter will be investigated with the Hosmer-Lemeshow goodness-of-fit test. Based on the results of the ROC curve analysis, we will proceed to identify different severity grades of acute appendicitis each one related to a specific risk of developing delayed IAA. *χ*^*2*^ test will be assessed to compare categorical variables, and univariate logistic regression will be performed to provide hazard ratios for individual variables, identifying possible predictors of postoperative complication (IAA above all). All significant (*p* < 0.05) variables at univariate analysis will be included in a multivariate regression model in order to detect independent risk factors for the outcome and to estimate odds ratio and 95% confidence intervals.

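### The 1067 patients are presented as a power calculation, but the figure is the worst-case confidence-interval width for one overall proportion and gives no power for either endpoint

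*Protocol article*

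**What the plan says.** The sample size is justified in the protocol article under *Data collection and statistical analysis*. That section notes that "The incidence of IAA after laparoscopic appendectomy reported in the literature ranges from 1.5 to 20" per cent, calls this interval too wide to ignore, and adds that incidence by severity and contamination has not been studied systematically. It then states that the "sample size for power calculation can be reasonably estimated given a 95% confidence interval", with z = 1.96, "a 50% standard deviation, and a 0.03 margin of error". It adds: "This formula does not include the incidence rate of IAA for the aforementioned reasons". The result is: "The estimated sample size would be around at least 1067 patients". The same section says that patients will be grouped by grade and contamination, by lavage or suction alone, and by abscess outcome.

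The endpoints are in *Hypothesis, design of the study, and aims*. The primary is "Relationship among each severity grade of acute appendicitis and postoperative incidence of intra-abdominal abscesses". The secondary is "Impact of intraperitoneal irrigation or suction alone on the incidence of IAA for each severity grade".

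**The concern.** The inputs listed are those of a precision formula for a single proportion. A power calculation needs a difference to be detected and a probability of detecting it, and neither is given. Neither endpoint is a single overall proportion: one compares incidence across grades, the other compares two operative practices inside each grade.

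This is not a detail that a condensed article leaves to a fuller document. The article does give a justification, and gives it the wrong label. A reader who takes 1067 to have come from a power calculation may assume that the study was sized for the grade-by-grade irrigation question, and so read an unremarkable within-grade result as evidence that irrigation makes no difference. The *Conclusions* section makes this a live risk, because it names the identification of scenarios in which the impact of irrigation is clear as the biggest practical consequence of the score.

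**Working it through.** **Inputs from the protocol article:** z = 1.96; standard deviation 0.5; margin 0.03; total 1067; cited abscess incidence 1.5% to 20%. **Not given:** power, target difference, number and size of grades, share of patients irrigated.

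**1. Reproducing 1067.** n = z² × SD² / d² = 1.96² × 0.5² / 0.03² = 3.8416 × 0.25 / 0.0009 = 1067.1. The arithmetic is right. For a binary outcome SD = √(p(1 − p)), which equals 0.5 only at p = 0.50, its maximum. So 1067 is the number for a 95% confidence interval of at most ±3 points around one proportion in the whole cohort.

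**2. What 1067 gives for the overall incidence.** Half-width = 1.96 × √(p(1 − p)/1067).

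| Incidence | Half-width with 1067 | Expected abscesses | n needed for ±3 points |
|---|---|---|---|
| 1.5% | ±0.7 points | 16 | 63 |
| 20% | ±2.4 points | 213 | 683 |

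**3. Precision within a grade (primary endpoint).** Assumption: four equal grades, one per appendix aspect in Table 1, so 1067/4 ≈ 267 each. Half-width = 1.96 × √(p(1 − p)/266.75), which is ±1.5 points at 1.5% and ±4.8 points at 20%. Setting the half-width to 0.03 gives p(1 − p) = 0.0009 × 266.75 / 3.8416 = 0.0625, so p ≈ 6.7%. Under this split the 3-point margin holds in a grade with incidence up to about 6.7% and fails above that.

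**4. Power across grades (primary endpoint).** Same four equal grades, chi-square test with 3 degrees of freedom, 5% level. The non-centrality is 266.75 × Σ(pᵢ − p̄)² / (p̄(1 − p̄)).

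| Assumed incidence in the four grades | Non-centrality | Power |
|---|---|---|
| 3, 4, 5, 6% | 3.1 | about 28% |
| 2, 3, 5, 8% | 13.0 | about 87% |
| 1.5, 3, 5, 10% | 23.7 | about 99% |

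**5. Power for irrigation versus suction within one grade (secondary endpoint).** Further assumption: 1:1 split, so about 133 v 133. Power = Φ[(|p₁ − p₂| − 1.96 × SE₀)/SE₁], where SE₀ uses the pooled proportion and SE₁ the separate ones, two-sided 5%. For 20% v 10%: SE₀ = √(2 × 0.15 × 0.85/133.4) = 0.0437; SE₁ = √((0.16 + 0.09)/133.4) = 0.0433; (0.10 − 1.96 × 0.0437)/0.0433 = 0.33; Φ(0.33) = 0.63.

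| Halving within a grade | Power, 133 v 133 |
|---|---|
| 20% to 10% | about 63% |
| 10% to 5% | about 34% |
| 5% to 2.5% | about 19% |

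For comparison, 80% power would take 199 per group for the first row and 435 per group for the second, in each grade.

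**The case against.** The best defence is that 50% is a deliberate worst case. The authors say openly that the published range is too wide to rely on, and the bound from p = 0.50 is valid whatever the true incidence. That stands. A reader might infer that the plan forecasts an incidence of 50%, or that its statement about leaving the incidence out is false. The text does not support that: no estimate of abscess incidence enters the formula, and the 50% stands in for one. What is missing is a sentence saying so. The defence also reaches only the overall incidence, which is not an endpoint.

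A second tempting reading is that the 3-point margin fails in every subgroup. It does not. Under four equal grades it is met at low incidence, as step 3 shows. The margin is simply not guaranteed within grades.

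A third is that the study is underpowered. For the primary comparison this cannot be concluded, since step 4 runs from about 28% to 99% according to the assumed gradient. For the secondary comparison the figures rest on four equal grades and a 1:1 split, neither of which the plan fixes. The analysis section says that severity grades will be identified from the ROC results, so their number and size are not yet known. For the same reason nothing shows that every combination of appendix aspect and contamination type would be analysed as a separate cell, and no figures are given for such cells.

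Finally, 1067 is stated as a minimum, and the *Discussion* concedes that a randomised trial would be the optimal design for the irrigation question. Both are fair points, but neither makes the figure a power calculation.

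**Conclusion.** The point holds as a misdescription of the trial's only sample-size justification. The arithmetic is correct; the property claimed for it is not. What 1067 secures is a 95% interval no wider than ±3 points for the overall incidence, and in fact ±0.7 to ±2.4 points over the cited range. It states nothing about power for either endpoint.

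The consequence is clearest for the secondary endpoint, where even a halving from 20% would be detected with only about 63% power under the assumed split, and smaller absolute differences with much less. Unequal grades would generally make the smaller ones less precise. For the primary endpoint the conclusion is only that power is unstated and depends strongly on the gradient.

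**What to change.** Keep 1067 and restate what it delivers, for example: *A sample of 1067 gives a 95% confidence interval of at most ±3 points for the overall IAA incidence (worst case p = 0.50; ±0.7 to ±2.4 points at 1.5–20%); it is not a power calculation for the primary or secondary endpoint.*

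Beside the sentence on leaving the incidence out, explain that 50% is the conservative bound used in place of an incidence estimate.

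Add a short scenario table, with grade sizes and irrigation share marked as assumptions, showing per-grade precision, power across grades for a few gradients, and the detectable irrigation difference within a grade. It has to be a scenario table, because the grades themselves are to come from the data.

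The cost is a few sentences and one small table. The stated figure will look less favourable, but no extra patients are needed.
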